## Statistical methods

### Statistical methods for primary and secondary outcomes

The primary outcome as the percentage of adolescents who successfully engage and secondary outcomes of the percentage who are retained within the adult health care services will be described using a 90% exact binomial confidence interval. If the lower confidence limit is less than or equal to 70%, the TMApp would not be considered effective in terms of increasing rates of engagement and retention within the adult services.

Participant demographics, clinical characteristics and study outcomes will be described using standard methods, including frequencies and percentages for categorical variables, and mean, standard deviation, median, quartiles and range for continuous variables. Kaplan-Meier methods will be used for time-to-event variables. Study outcomes will be described in the total cohort as well as by chronic illness group, acknowledging that sub-group numbers will limit further analyses.

Linear, logistic or proportional hazards regression models will be used to examine predictors of study outcomes including TMApp use, age, gender, illness, transition readiness and mental health status in univariate models and models adjusted for potential confounders including other transition programs, use of other applications and deterioration in illness control. All effects will be presented with confidence intervals where possible.

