#### Secondary objectives

To examine the rates of retention with adult services at 12 and 18 months in young people with a chronic illness who have successfully transitioned (i.e. successfully engaged) to adult services.To understand how disease control changes during the first 18 months post transitionTo understand if the use of the TMApp can assist with preventing deterioration of chronic illness control in young people in the 12 months post transition.

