#### Engagement and retention with adult service

Successful engagement with the adult service at 6 months will be defined as confirmed attendance at least one appointment with the adult service by six months post discharge from paediatric care (i.e. after the last paediatric appointment). This will be considered as a *successful transfer* to adult services. This number is chosen because most chronic conditions have guidelines on the optimal number of specialist visits per year with a frequency varying from 3 to 6 months. Routine annual visits are less likely and will be recorded as such.

*Engagement* with the adult service will be assessed, with consent of the young person/parent, (provided at enrolment) via phone call to the young person and nominated adult service at 6 months post discharge from paediatric care. If the young person has not attended the service they were referred to, they will be asked if they are attending an alternate service and for consent to contact this service. Young people who cannot be contacted at 6 and 12 months post discharge from the paediatric service will be considered to have unsuccessful engagement and be a *failed transfer* to adult care.

*Retention* within the adult service will be defined as at least one confirmed attendance with the adult service in the preceding 6 months at 12 and 18 months follow up. These data will be collected, with consent, via phone call to the young person and the adult service to obtain information regarding attendance at the adult service at 12 and 18 months follow up. Young people who cannot be followed up at 12 and 18 months post discharge from the paediatric service will be considered to not be retained by the adult service (*failed retention*).

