### Sample size

#### Numbers required (power analysis)

There is limited empirical evidence on the effectiveness of current transition programs in regard to engagement with and retention in adult services or on rates of deterioration in illness control on which to base power calculations. In the diabetes literature, approximately 70% of adolescents will make some form of transition from paediatric to adult services [23, 24]. Using a predicted attrition rate of 30%, a sample size of 70 participants will be needed to obtain the minimum sample of 49 adolescents required for this study. A sample of 49 adolescents will have greater than or equal to 80% power at 5% one-sided alpha, to detect an increase in the rate of successful transition from paediatric to adult care from 70%.

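### The 70% rule is also applied to 12- and 18-month retention, for which the protocol gives no reference rate and no settled denominator or definition

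*Protocol article*

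**What the plan says.** **The rule.** Under Statistical methods for primary and secondary outcomes, the percentage engaged (primary) and the percentages retained (secondary) are each described with a 90% exact binomial interval. One rule covers both: if the lower limit does not exceed 70%, the app "would not be considered effective in terms of increasing rates of engagement and retention within the adult services".

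**Where 70% comes from.** The power analysis reports from the diabetes literature that "approximately 70% of adolescents will make some form of transition from paediatric to adult services". It powers the study for successful transition only: "A sample of 49 adolescents will have greater than or equal to 80% power". It describes the evidence on engagement, retention and deterioration as limited. No retention rate appears anywhere in the article.

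**Whose retention.** The secondary objective is retention at 12 and 18 months "in young people with a chronic illness who have successfully transitioned (i.e. successfully engaged) to adult services". The Secondary outcomes section instead reviews attendance of the participants, without that restriction. Under Engagement and retention with adult service, the failure rule reads: "Young people who cannot be followed up at 12 and 18 months post discharge from the paediatric service will be considered to not be retained". It too is not limited to those who engaged. The statistical section names no denominator.

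**What counts as retention.** The Definitions and the Secondary outcomes require a *further* attendance in the preceding 6 months. The section on engagement and retention requires one confirmed attendance in the preceding 6 months and omits *further*.

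**The concern.** A one-sample comparison needs a null value that describes the same endpoint, in the same population, under usual care. For 6-month engagement, 70% at least refers to a related quantity. For retention, the protocol offers nothing that says what 70% stands for.

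The meaning of the threshold also changes with the denominator. Among those who engaged, usual retention could well be above 70%, and the threshold could then be cleared with no benefit from the app. Among all participants, with prior engagement required, usual retention would be below the usual engagement rate. The threshold would then be stricter than the historical rate, and a real improvement could be called not effective. Since the protocol does not settle the denominator or the definition, the choice could be made after the data are seen.

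**Working it through.** **Inputs from the protocol.** Threshold 70%; 90% exact interval, so a one-sided 5% lower limit; 70 recruited; 30% attrition; 49 evaluable; power at least 80%.

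**Inputs assumed (not in the protocol).** Retention among the engaged of 80% to 100%; true engagement of 85% where an improvement is illustrated; 60 of 70 engaged in the example of a reversed verdict.

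**Formulas.** For x successes of n, the lower limit is the 5% quantile of a Beta(x, n − x + 1) distribution. The rule is cleared at the smallest x whose lower limit exceeds 0.70. The chance of clearing it at true rate p is P(Bin(n, p) ≥ x).

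**1. The plan's own figure.** 49 / (1 − 0.30) = 70. With n = 49 the rule needs 40 (81.6%, lower limit 70.1%); 39 gives 67.9%. The exact one-sided error at 70% is 0.048. Power is 0.81 if the true rate is 85%. The alternative is not stated, but 85% reproduces the claim of at least 80%. The sample size for engagement is not at fault.

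**2. The denominator can reverse the verdict.** Suppose 60 of 70 engage.

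| Denominator | Needed to clear 70% | Lower limit | One fewer |
|---|---|---|---|
| Engaged only, n = 60 | 49 (81.7%) | 71.5% | 48: 69.6% |
| All enrolled, n = 70 | 56 (80.0%) | 70.5% | 55: 68.9% |

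With 49 retained, the lower limit is 71.5% of 60 but 59.7% of 70. Every count from 49 to 55 clears the threshold among the engaged and fails among all enrolled.

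**3. Engaged-only, app has no effect.** Engagement stays at 70%, so 49 of 70 engage and 40 retained are needed. P(Bin(49, r) ≥ 40) for assumed usual retention r:

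| r | Chance of clearing 70% |
|---|---|
| 80% | 0.47 |
| 85% | 0.81 |
| 90% | 0.98 |

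The one-sided error for which the study was sized is 5%.

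**4. All enrolled, prior engagement required, engagement truly raised to 85%.** The overall rate is 0.85 × r, and 56 of 70 are needed:

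| r | Overall rate | Chance of clearing 70% |
|---|---|---|
| 80% | 68.0% | 0.02 |
| 85% | 72.3% | 0.09 |
| 90% | 76.5% | 0.30 |
| 95% | 80.8% | 0.63 |
| 100% | 85.0% | 0.91 |

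On the same reading, the rate with no effect at r = 90% would be 0.70 × 0.90 = 63%, so 70% is not the null value.

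**5. The definition matters too.** If *further* is dropped, someone who first attends after month 6 can count as retained. In the 90% row of step 4, let 20% or 50% of the non-engaged (assumed) attend for the first time in months 6 to 12. The overall rate is then 0.765 + 0.15 × 0.20 = 79.5%, or 0.765 + 0.15 × 0.50 = 84.0%, and the chance of clearing 70% rises from 0.30 to 0.53 or 0.86. The no-effect rate becomes 0.63 + 0.30 × 0.20 = 69%, or 0.63 + 0.30 × 0.50 = 78%.

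**The case against.** Several points on the other side have force.

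- **The denominator may be less open than it looks.** The objective names those who engaged, and *further* attendance agrees with it. The rule for people who cannot be followed up could operate within that group. A reader might infer a flat contradiction; the text supports only that the sections are inconsistent and the matter is unresolved. The analysis set of a secondary endpoint may also be left to an analysis plan not shown here. That does not rescue the threshold, which the article states together with its only source.
- **Retention need not be bounded by 6-month engagement.** A reader might infer that retention among all enrolled can never exceed engagement. That holds only where prior engagement is required. Without *further*, late first attenders count, as step 5 shows.
- **The probabilities rest on assumed rates.** The 0.30 in step 4 should not be read alone: the range is 0.02 to 0.91. Low power on a secondary endpoint for which the study was not sized is in itself no error.
- **The rule says only when the app is not effective.** It never states that exceeding 70% proves effectiveness for retention. This is correct, and a positive verdict is implied rather than written. A not-effective verdict against a value with no basis is nevertheless just as hard to defend.

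None of this supplies a reference rate for retention.

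**Conclusion.** The point holds in a limited form. As written, the plan judges 12- and 18-month retention against a value whose only stated basis is the share making some form of transition. The effective or not-effective verdict on retention therefore has no valid reference value. This conclusion depends on none of the assumed rates.

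The unsettled denominator and definition add to it, because in a plausible case (60 of 70 engaged) any count from 49 to 55 retained gets opposite verdicts. The probabilities in steps 3 to 5 are illustrations under assumed rates and show direction and possible size only.

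A reader might go further and conclude that the retention results cannot be interpreted at all. The protocol does not support that: once the denominator and definition are named, the percentage and its interval are sound descriptive results. Retention is secondary, and neither the primary engagement analysis nor its sample size is affected by this point.

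**What to change.** - Limit the 70% decision rule, and any wording about effectiveness, to engagement at 6 months.
- Report retention at 12 and 18 months descriptively, with exact 90% confidence intervals and no threshold.
- Use one definition of retention throughout, stating whether a first attendance after month 6 counts.
- Show retention both among those engaged at 6 months, as in the secondary objective, and among all enrolled, each labelled. Which comes first is a matter of choice: the engaged group is selected on an outcome that the app is meant to change, so an all-enrolled main presentation is equally defensible.

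The cost is wording only. No new data, sample size or procedure is needed. The sponsor gives up a threshold-based verdict on retention.

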### Trial design

The trial is designed to be a two centre, pragmatic, single arm, mixed methods cohort study. As this is a single arm study, there will be no randomisation or allocation process on recruitment. Results will be compared with existing historical data from our previous research as well as others.

Source of historical data from the following source:Perry L, Steinbeck KS, Dunbabin JS, Lowe JM. Lost in transition? Access to and uptake of adult health services and outcomes for young people with type 1 diabetes in regional New South Wales. Med J Aust 2010 Oct;193(8):444–9.Audit of 239 young adults aged 18–28 years with type 1 diabetes accessing five adult diabetes services before 30 June 2008 in three geographical regions of New South Wales [23]Garvey KC, Markowitz JT, Laffe LMB. Transition to Adult Care for Youth with Type 1 Diabetes. Curr Diab Rep 2012 Oct;12(5):533–541 [24].Data were collected between August 2004 and October 2005 through face-to-face interviews with over 200 clinicians in 68 clinical services in tertiary paediatric hospitals in New South Wales, providing information on approximately 4200 patients

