##### Intervention: downloading and use of the TransitionMate mobile phone application to assist transition of adolescent from paediatric to adult clinic services

The TransitionMate mobile phone application will be downloaded onto the participant’s mobile phone once the study has been explained and consent has been obtained. Download is performed by the participant under the guidance of the researcher. The download will be available from the Apple Store (ios) or Google Play Store (android). Use of the application would involve the participant independently opening the mobile application and using the features within. These features are:

*To do list*

*Measures of illness control*

*Contact list*

*Medication Lists*
*Images* (Take and save photos)
*Mood tracker using words or emojis*

The number of times the intervention (TMApp) and the features are used is determined by each participant. TMApp usage will be reviewed at the 6, 12 and 18 months by follow up phone calls (Additional files 4, 5, 6). These self-report data can be broadly compared to the application data analytics, which are cohort only data. Up to 5 attempts will be made to contact each participant via a telephone call at each of the 6, 12 and 18 months’ time points. A SMS message will be sent if the call is not picked up with contact details provided for a return call when it is convenient for the participant. Participants will no longer be contacted should they express at any time that they would not like any further communication with regards to the study.

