### Other data collection

The following data will be collected at baseline: gender, date of birth, ethnicity, diagnosis, young person’s email and mobile phone number, and one parent’s contact number and email (Additional file 8). We will record the standard transition care which the young person has received. Established transition services in our patient population includes ACI Transition Care Service, Trapeze Transition Service [25, 26] and joint paediatric and adult clinics. The NSW Health Agency for Clinical Innovation (ACI) Transition Care Service is a state-wide care coordination service responsible for supporting young people (aged between 14 and 25 years) with chronic illness/disability as they move from children’s health services to adult health services. Trapeze is part of the Transition Care Network and provides a supported transition into adult care for patients aged 14–25 within the Sydney Children Hospital Network. We will also obtain the details of the adult service that the treating paediatric team has referred the young person to. Included in the consent is collection of EMR data on measures of illness control and frequency of visits to the paediatric service in the previous 12 months.

Table 1 shows a sample list of conditions and relevant illness markers compiled in consultation with on the Clinical Services which have agreed to take part in the study. If other conditions not mentioned here are included, the research team will determine the preferred control marker in consultation with the respective clinical team.

**Table 1 Tab1:** Sample list of illness markers for chronic illnesses

Chronic illness	Illness marker
Acquired brain injury	Functional Independence Measure (FIM), the Glasgow Outcome Scale (GOS), and the Disability Rating Scale (DRS)
Autoimmune thyroid disease	Free T4; Free T3; TSH
Congenital Adrenal Hyperplasia	17 OHP; Plasma Renin Ratio; Testosterone, Androstenedione, Dehydroepiandrosterone sulfate (DHEAS)
Cystic fibrosis	FEV_1_; Weight
Duchenne muscular dystrophy	Creatinine kinase; Lung function test; GMFCS
Epilepsy	Number and frequency of seizures
Inflammatory bowel disease - Crohn’s, Ulcerative colitis	Weight; CRP; Faecal Calprotectin; ESR
Diabetes (Type 1 and 2)	HbA1c
Chronic liver disease, including Glycogen storage disorders and Transplant	Liver function tests and albumin level
Phenylketonuria	Serum Phe and tyrosine levels
Systemic lupus erythematosus	Antinuclear antibodies

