### Outcomes

#### Primary outcome

To measure engagement with adult services, we will review attendance of the participants at adult appointments at 6 months. Engagement is defined by at least one attendance to the adult service in the preceding 6 months at the 6 months follow-up. This is obtained from the adult service or patient self-report via study-specific questionnaires. (Questionnaires in Additional files) and will be supplemented by information from hospital databases. TMApp analytics will provide further information on the TMApp usage.

Time point: At 6 months after last clinic appointment at paediatric service.

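### Paediatric visit frequency over the previous 12 months is collected but not named among the model terms, so the app-use coefficient for engagement and retention may be confounded by past attendance

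*Protocol article*

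**What the plan says.** Under Other data collection, the Protocol article states that the consent covers "collection of EMR data on measures of illness control and frequency of visits to the paediatric service in the previous 12 months". No other section gives visit frequency a use in the analysis.

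The Primary outcome section says: "Engagement is defined by at least one attendance to the adult service in the preceding 6 months at the 6 months follow-up". Retention is further attendance, judged at 12 and 18 months.

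There is no allocation: "As this is a single arm study, there will be no randomisation or allocation process on recruitment". Exposure within the cohort is self-selected: "The number of times the intervention (TMApp) and the features are used is determined by each participant".

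The section on statistical methods for primary and secondary outcomes sets out regression models for "predictors of study outcomes including TMApp use, age, gender, illness, transition readiness and mental health status in univariate models", followed by "models adjusted for potential confounders including other transition programs, use of other applications and deterioration in illness control". Both lists are introduced by *including*, so neither is closed. The effectiveness rule in the same section is separate. It compares the lower limit of a 90% exact binomial interval with 70% and uses no regression model.

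**The concern.** The outcome is attending a clinic, and the trial holds a baseline record of the same behaviour. A young person who attends reliably may be more likely both to use a self-management app and to turn up at the adult clinic. If so, app users will engage more often than non-users even if the app does nothing.

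These regressions are the only described analysis that relates app use to engagement or retention inside the cohort. With no concurrent control group, readers will look to that coefficient for a sign that the app helps.

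The named confounders include deterioration in illness control. Under Measures of illness control this is assessed at 6, 12 and 18 months, after app use has begun. A participant with no marker obtainable from the adult service is also counted as deteriorated, so the variable can partly encode non-attendance itself. The plan thus names a post-exposure variable and does not name a pre-exposure one that it already collects.

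**Working it through.** **1. The plan's own figures, to show what is not affected.** The sample size section gives "A sample of 49 adolescents will have greater than or equal to 80% power at 5% one-sided alpha" against a benchmark from the diabetes literature that "approximately 70% of adolescents will make some form of transition from paediatric to adult services", with 30% attrition.

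- Recruitment: 49 / (1 − 0.30) = 70, as stated.
- Exact test at n = 49: the smallest r with P(X ≥ r | p = 0.70) ≤ 0.05 is r = 40 (81.6%), exact alpha 0.048.
- Power: the alternative rate is not stated. An assumed 85% gives 0.809, consistent with the claim.

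None of this involves a covariate, so adding one changes neither the sample size nor the primary decision.

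**2. How large a false app effect could be.** The documents give no association between past attendance, app use and engagement, so the inputs here are assumptions. Half the cohort are regular attenders, the app has no effect, and overall engagement is 70%. Let e1, e0 be engagement and u1, u0 app use in regular and irregular attenders.

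- Engagement in users: E_u = (u1·e1 + u0·e0) / (u1 + u0)
- Engagement in non-users: E_n = [(1−u1)·e1 + (1−u0)·e0] / [(1−u1) + (1−u0)]
- Odds ratio = [E_u/(1−E_u)] / [E_n/(1−E_n)]

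Worked example, e = 85%/55% and u = 60%/40%: E_u = 0.6×0.85 + 0.4×0.55 = 0.73; E_n = 0.4×0.85 + 0.6×0.55 = 0.67; odds ratio = (0.73/0.27)/(0.67/0.33) = 1.33.

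| Engagement, regular/irregular | App use, regular/irregular | E_u | E_n | Null odds ratio |
|---|---|---|---|---|
| 75/65 | 60/40 | 0.71 | 0.69 | 1.10 |
| 80/60 | 50/40 | 0.711 | 0.691 | 1.10 |
| 85/55 | 60/40 | 0.73 | 0.67 | 1.33 |
| 85/55 | 60/30 | 0.75 | 0.659 | 1.55 |
| 85/55 | 70/30 | 0.76 | 0.64 | 1.78 |
| 90/50 | 70/30 | 0.78 | 0.62 | 2.17 |
| any of these | 50/50 | 0.70 | 0.70 | 1.00 |
| 85/55 | 40/60 (reversed) | 0.67 | 0.73 | 0.75 |

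Within each attendance stratum the odds ratio is 1.00 by construction.

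**3. What that does to a test.** Simulated cohorts of 70, one-sided 5% test of app use in a logistic model with no other covariate:

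- Odds ratio 1.33 (85/55, 60/40): false positives about 13% to 15%.
- Odds ratio 1.78: about 28% to 30%.
- Odds ratio 2.17: about 41% to 44%.
- Odds ratio 1.10 (75/65, 60/40): about 7%.

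Adjusting for the exact attendance variable that generated the data returns the first three to about 4% to 6%, as it must. If the recorded variable classifies reliable attenders correctly only 70% of the time (an assumption), the adjusted rates in those three scenarios are still about 12%, 24% and 36%.

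**4. Room in the model.** At 70% engagement the number of non-engagers is 0.30 × 49 = 14.7 to 0.30 × 70 = 21, or about 15 to 21. Nine terms are already named (six predictors and three confounders).

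**The case against.** **The lists are open.** This stands. A full protocol or SAP could add the variable, so a reader should not infer that past attendance is excluded from every model. What can be said is that the article names specific confounders and does not name the most direct one it collects.

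**No effectiveness rule uses these models.** This also stands. The decision rests on the exact interval against 70%. The one stated objective that links app use to an outcome within the cohort concerns illness deterioration, for which past attendance is not the baseline counterpart. The point is therefore confined to the secondary regressions of engagement and retention on app use.

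**Direction and size are assumed.** A reader might infer that the coefficient must favour the app. The documents do not show that regular attenders use the app more, and the reversed case gives 0.75. Recruitment largely through clinics may also under-represent poor attenders and narrow the contrast. Transition readiness and other transition programs, both listed, may absorb part of the effect, though neither measures attendance.

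**Visit frequency is not reliability.** The count partly reflects the illness schedule: the engagement section describes specialist visits every 3 to 6 months for most conditions, with annual visits less likely. No section says that scheduled visits are captured. A reader might infer from the simulation that adding the variable removes the bias, but the misclassification result shows that it may remove only a small part.

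**App use itself is poorly measured.** App analytics are cohort-only, so individual use comes from self-report at follow-up calls. That is a separate limit on the same models, and this change does not address it.

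**Conclusion.** The concern holds in a limited form. The Protocol article collects a plausible pre-exposure confounder of app use and attendance and does not name it in the models that relate the two. The app-use coefficient for engagement and retention may therefore be confounded, more likely upwards than downwards. That direction rests on the judgement that organised attenders are also more willing app users, not on any figure in the documents.

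The size cannot be derived from the plan. Under the assumed inputs that favour the app, the null odds ratio lies between about 1.1 and 2.2; it is 1.0 if app use and past attendance are unrelated. The documents do not support the stronger readings that the variable is barred from all models, that the primary conclusion is biased, or that adjustment would fully cure the problem. This is a low-cost improvement to a secondary analysis.

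**What to change.** In the section on statistical methods for primary and secondary outcomes, state that the adjusted models of engagement and retention on TMApp use will include paediatric attendance in the 12 months before enrolment as one term. Fit it together with illness, so that differences in visit schedule between conditions are not read as differences in reliability. If the EMR holds both, use visits attended as a share of visits scheduled.

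To hold the number of terms, let it replace deterioration in illness control in those models, because deterioration is measured after app use begins. Report the app-use effect with and without past attendance, and describe the result as an association.

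Cost: a sentence or two of analysis wording. The visit count needs no new data; the attended share does only if scheduled visits are not already in the record. The term uses one degree of freedom in a model with about 15 to 21 non-engagers, which the swap offsets. Residual confounding will remain because visit count is an imperfect measure of reliable attendance, and the report should say so.
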